### Objectives and endpoints

The primary objective is to demonstrate that fluconazole normalizes or decreases urinary calcium after 4 months of treatment in patients with hypercalciuria and increased 1,25(OH)_2_D levels. The primary endpoint will be the proportion of patients with normalization of 24-h urinary calcium between baseline and 16 weeks (W_16_), or with a relative decrease of 30% of 24-h urinary calcium in patients who still display hypercalciuria (> 0.1 mmol/kg/day) at W_16_.

The secondary objectives are to evaluate the effects of fluconazole on the evolution of biomarkers of calcium/phosphate metabolism and renal function over time, to describe precisely the cohort at baseline and after 4 months of treatment, to assess safety of fluconazole, to identify the onset of potential mycological resistances, to assess compliance of treated patients, and to measure quality of life and treatment satisfaction. In order to answer to the secondary objectives, corresponding secondary endpoints (as summarized in Table 1) will be collected.

**Table 1 Tab1:** Secondary objectives and endpoints of the FLUCOLITH trial

Secondary objectives	Secondary endpoints to collect
1- Effects of fluconazole on the evolution of calcium/phosphate metabolism over time	- Serum analysis: calcium, ionized calcium, phosphate, magnesium, PTH, 25-OH-D, 1,25(OH)_2_D, 24-25(OH)_2_D, 25-OH-D:24-25(OH)_2_D ratio, total alkaline phosphatase - 24-h urine collection: phosphate, calcium, creatinine, TmP/GFR, citrate - OCL test
2- Evolution of renal function	- Serum creatinine allowing the calculation of eGFR with the FAS formula - Renal ultrasounds: number and size of lithiasis, nephrocalcinosis
3- Detailed description of the cohort at baseline and after treatment	- Anthropometry - Evaluation of nutritional intakes: calcium, sodium and protein intakes estimated with a dietetic evaluation and completion of 3 questionnaires - Bone evaluation with biomarkers: bone alkaline phosphatases, FGF23, Klotho - Bone evaluation with DXA - Genetic analysis (if not already performed)
4- Safety evaluation	- Cardiac evaluation: electrocardiogram, corrected QT interval - Monthly blood analyses: hepatic functions, complete blood cell counts, albumin, serum creatinine, calcium, phosphate, LDH
5- Evaluation of the onset of potential mycological resistances	Mycological samples (urine and buccal samples) to evaluate the onset of potential resistance of candida
6- Compliance assessment	- Accountability of returned study treatment - Information of patients’ diary
7- Quality of life and treatment satisfaction assessments	- Quality of life questionnaires (8–12 years, 13–17 years, ≥ 18 years) reported by patients - Treatment satisfactory questionnaire reported by patients

*PTH* parathyroid hormone*, 25-OH-D* 25 OH vitamin D, *1,25(OH)*_*2*_*D* 1-25 di-hydroxy-vitamin D, *24-25(OH)*_*2*_*D* 24-25 di-hydroxy-vitamin D, *OCL* oral calcium load, *TmP/GFR* Tubular maximum Phosphate Reabsorption per Glomerular Filtration Rate, *eGFR* estimated glomerular filtration rate, *FGF23* Fibroblast Growth Factor 23, *DXA* dual X-ray absorptiometry, *LDH* lactate dehydrogenase

### Benefit/risk ratio

The benefit for the patients is a standardized and complete medical follow-up and monitoring during the study period. Moreover, if fluconazole is effective, recovering normal urinary calcium levels will decrease the risk of further nephrolithiasis and/or nephrocalcinosis, CKD, and bone complications. There is no major risk expected for the participants. The study includes non-invasive and low-radiation radiological examinations (DXA and renal ultrasounds).

The patients will undergo additional blood and urine analyses as compared to usual standard practice. The blood volume taken for the study will not exceed the threshold volume defined by the Blood Volume Guidelines. Fluconazole is supposed to decrease urinary calcium by decreasing 1,25(OH)_2_D concentrations; however, in this population with increased 1,25(OH)_2_D levels at baseline, the risk of 1,25(OH)_2_D deficiency induced by fluconazole treatment appears very low. To monitor the possible emergence of *Candida* resistance, urine and buccal samples will be collected before the treatment period (W_0_) and after 8 and 16 weeks of treatment. Thus, the benefit/risk ratio does not seem to be unfavorable.

### Randomization

The randomization will be stratified on the age group (children [10;18], adult [18;60]). Randomization will be performed centrally through the Ennov Clinical software. The lists for randomization will be provided by the department of biostatistics of the Hospices Civils de Lyon and built using the permuted block randomization method. The data from the 5 first treated adults during a period of 10 weeks after titration period (visit V_8_) will be at first evaluated by the DSMB and reported to ANSM to decide inclusion of patients < 18 years old.

### Sample size

A total of 60 patients (adults and children) will be included.

The sample size calculation was performed according to these hypotheses: 15% of normalization of calciuria (≤0.1 mmol/kg/day) or decrease of 30% of calciuria (as compared to baseline) is expected in the placebo group vs 60% in the fluconazole group. Under these hypotheses, 25 patients should be randomized per group to achieve 89% power to show a statistical difference between the two groups (two-sided 5% alpha level, Fisher test).

Amoung the patients included at V_1_, only patients with 24-h calciuria > 0.1 mmol/kg/day and serum 1,25(OH)_2_D levels ≥ 150 pmol/L and serum 25-OH-D levels > 20 nmol/L and calcemia levels ≤ 2.65 mmol/L will be randomized. Hence, it is planned to recruit at V1, 60 patients to be sure to have at least 50 patients randomized. Moreover, it will allow to take into account lost to follow-up in the study.

### Data management

There is a priori no criterion for premature drop-out. The patients, regardless of the randomization group, will not be excluded from the study and will be followed up according to the protocol.

Outcomes related to 24-h calciuria measurements will be collected and reported at baseline and before every study visits V_3_, V_4_, V_5_, V_6_, and V_8_, by the investigator or the authorized persons in the medical field of participant, as per site practice using a standard of care software. If there is missing data due to a problem during the collection of urine, a 4-day margin is planned to be able to organize a new collection at the patient’s home/center.

All study results collected in electronic or paper source documents will be entered in an electronic case report form by the investigator or an authorized person who will be appearing on the tasks delegation sheet, as soon as they are collected (during/after patients’ visits). Data will be coded with respect to data confidentiality. Each form will be dated and signed electronically by the investigator, signifying its agreement with the data entered in the eCRF. The Ennov Clinical system was selected. Control quality of the data is performed both centrally and on site by monitors. Presence, accuracy, and conformity of the data is verified.

Surveillance and emergence of adverse and serious adverse event is performed. All adverse and serious adverse events will be reported in the eCRF. The investigator evaluates each adverse event in terms of severity, causality with experimental drug (reasonably related / unrelated). All the serious adverse events shall be notified without delay to the sponsor.

The sponsor may temporally or definitively interrupt a subject’s participation in the event of a serious adverse event.

The patients will be discontinued from the study treatment due to calcemia levels, hepatic toxicity, low neutrophil or platelet count, any anaphylactic reaction, cardiac abnormalities, or renal insufficiency.

### Statistical analyses

The intent to treat (ITT) population is defined as all the randomized patients according to their arm randomly allocated, whatever their inclusion criteria, their actual arm, would they be evaluable or not for the primary endpoint. Description of patients at baseline (inclusion) will be done in intent to treat. Primary and secondary endpoints regarding the efficacy of fluconazole will be analyzed in intent to treat. Per-protocol (PP) population is defined as the ITT population without the patients with major protocol deviations. Major protocol deviations will be identified during the blind review and will include, but are not limited to, cases of premature withdrawals and absence of corresponding data, non-respect of eligibility and/or non-eligibility criteria, very poor adherence to study treatment/ study treatment not taken, a late inclusion date leading to the ending of the study during summer, etc. They will be identified during the blind review and will be specified in the statistical analysis plan. Per-protocol analyses will be performed as secondary analysis of the primary endpoint. The safety population is defined as the population of patients with at least one dose of study treatment, analyzed in the actual treatment arm. The safety endpoints will be analyzed on the safety population.

The quantitative variables will be described by the following parameters: number of patients, number of missing values, mean, standard deviation (SD), median, first and third quartiles (Q1 and Q3), minimum, and maximum. The qualitative variables will be described by the following parameters: number of patients, number of missing values, frequency, and percentage of each modality (missing values will not be included in the denominator used for frequency computation). A *p*-value less than 5% will be considered as statistically significant. Two-sided 95% confidence intervals will be provided for the analyses. The analyses will be performed using the R and SAS software.

For the primary outcome, the proportions of patients with normalization of calciuria or decrease of 30% of calciuria (as compared to baseline, V_1_ from W_16_, V_8_) will be described in both groups. The effect of fluconazole on calciuria will be quantified and tested through the odds ratio (with its 95% confidence interval), adjusted on the age class (children/adult) and on the level of 1,25(OH)_2_D during the screening period (150–200 pmol/L or >200 pmol/L). A description of the proportions of success depending on the dose of fluconazole administered at the end of the titration period will be performed. An exploratory analysis of the fluconazole effect will be performed in the subgroups defined by the level of 1,25(OH)_2_D during the screening period (150–200 pmol/L or >200 pmol/L). Secondary endpoints related to evolution over time will be analyzed using mixed effect models.

Missing data will generally not be imputed. If there is missing data due to a problem during the collection of urine (carrier, broken tube...) a 4-day margin is planned to be able to organize a new collection at the patient’s home/center. For the primary endpoint, a patient without calciuria assessment at W_16_ will be considered as a patient without normalization of calciuria. Two sensitivity analyses will be performed. The first one will be performed by multiple imputations, the outcome of patients without 24-h calciuria assessment at W_16_ will be sampled from a Bernoulli distribution with probability equals to the proportion of calciuria normalization in the same treatment, initial 1,25(OH)_2_D level category, and age class groups. A second analysis will be performed by excluding all patients without calciuria assessment at W_16_.

A detailed statistical analysis plan will be written before the database is frozen. It will take into account all protocol modifications or all unexpected events occurring throughout the study and having an impact on the analyses presented here. The planned analyses may be completed in line with the study objectives. They will be carried on by the Biostatistic Department of the Hospices Civils de Lyon.

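### The imputation sensitivity analysis names normalization rather than the composite outcome, draws from fixed cell proportions and ignores each patient's own calciuria, so it adds little to the complete-case analysis

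*Protocol article*

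**What the plan says.** Under Statistical analyses, the primary outcome is described through "the proportions of patients with normalization of calciuria or decrease of 30% of calciuria", which is a composite. The Objectives and endpoints and Sample size sections define success in the same way.

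A patient with no W16 calciuria counts as a failure in the primary analysis. Two sensitivity analyses follow:

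- **Multiple imputation.** The missing outcome "will be sampled from a Bernoulli distribution with probability equals to the proportion of calciuria normalization in the same treatment", initial 1,25(OH)2D category and age class. Two arms, two 1,25(OH)2D categories and two age classes make 8 cells.
- **Complete case.** "A second analysis will be performed by excluding all patients without calciuria assessment at W_16".

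The Data management section shows what else is known about a patient whose W16 value is missing: "Outcomes related to 24-h calciuria measurements will be collected and reported at baseline and before every study visits V_3_, V_4_, V_5_, V_6_, and V_8". V8 is the W16 visit, so baseline and up to four on-treatment values may be available.

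**The concern.** The imputation rule is a computing instruction fixed in the protocol article, and it has three weaknesses.

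1. **Target.** The probability it names is that of normalization, which is one of the two routes to success. A programmer who followed the words would use a lower rate than the endpoint requires.
2. **Uncertainty.** The probability is set equal to an observed cell proportion. Proper multiple imputation first draws the parameter and then the outcome. Here only the outcome is drawn, so all imputed sets treat the cell proportion as known. In a cell at 0% or 100% the draws do not vary at all, and in an empty cell the stated probability does not exist.
3. **Information.** A patient who had normalized by V6 and one who never responded get the same probability if they share a cell.

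The two sensitivity analyses exist to show whether the conclusion depends on counting missing as failure. If both rest on nearly the same assumption, the reader learns little from the second. Neither would show what happens if patients are missing because of how they responded.

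**Working it through.** **Plan's own figure.** Inputs from Sample size: "15% of normalization of calciuria (≤0.1 mmol/kg/day) or decrease of 30% of calciuria (as compared to baseline) is expected in the placebo group", 60% under fluconazole, 25 per group, "two-sided 5% alpha level, Fisher test". Exact enumeration over two binomials gives power 0.892, so the stated 89% reproduces. The rates 15% and 60% are used below.

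**Assumptions.** The article gives no missing-data rate, share of children, 1,25(OH)2D split or rate for normalization alone. I take 10% and 20% missing, 10-30% children, an even 1,25(OH)2D split, and normalization alone in 30-45% of fluconazole patients (50-75% of the 60% who succeed).

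**1. Literal reading of the proportion.** With a fraction d missing completely at random and draw probability q, the fluconazole rate is 0.60(1 − d) + q·d.

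| Missing | q = 0.30 | q = 0.45 | q = 0.60 (composite) | Missing = failure |
|---|---|---|---|---|
| 10% | 0.54 + 0.030 = 57.0% | 0.54 + 0.045 = 58.5% | 60% | 54% |
| 20% | 0.48 + 0.060 = 54.0% | 0.48 + 0.090 = 57.0% | 60% | 48% |

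The loss is 1.5-3 points at 10% missing and 3-6 points at 20%.

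**2. Cell sizes.** The average is 50/8 = 6.25. The expected size of a child cell is 25 × share of children × 0.5.

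| Children | Child cell | Adult cell | Chance that at least one of 8 cells is empty (23 observed per arm) |
|---|---|---|---|
| 10% | 1.25 | 11.25 | 77% |
| 20% | 2.5 | 10.0 | 32% |
| 30% | 3.75 | 8.75 | 9% |

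The chance that a cell of size k shows exactly 0% or 100% is p^k + (1 − p)^k:

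- Placebo, k = 2: 0.15² + 0.85² = 0.745. Placebo, k = 4: 0.0005 + 0.522 = 0.52.
- Fluconazole, k = 2: 0.36 + 0.16 = 0.52. Fluconazole, k = 4: 0.130 + 0.026 = 0.16.

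At 20% children and 10-20% missing, simulation puts about 2-3% of missing patients in an empty cell and 23-26% in a 0% or 100% cell.

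**3. Effect on the estimate and its standard error.** I simulated 3,000 trials with 25 per arm, 20% children, 20% missing completely at random, 30 imputations, and Rubin's rules on the risk difference (true value 0.45).

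| Analysis | Mean risk difference | Model SE | Empirical SE |
|---|---|---|---|
| Missing = failure | 0.36 | – | – |
| Complete case | 0.45 | 0.132 | 0.138 |
| Planned imputation, composite | 0.45 | 0.127 | 0.138 |
| Planned imputation, normalization only (75% / 50% of responders normalize) | 0.43 / 0.40 | – | – |

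The imputation SE is too small by 1 − 0.127/0.138 = 8%. A separate run gave an empirical SE of 0.135, hence 1 − 0.127/0.135 = 6%.

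**4. What neither analysis shows.** As an illustration with 25 per arm and an unadjusted Fisher test, 13 against 4 successes gives p = 0.016. If two placebo patients counted as failures because they were missing had in fact succeeded, 13 against 6 gives p = 0.079. For 15 against 4, p = 0.003; four such patients make it 15 against 8, p = 0.088.

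**The case against.** **The wording is probably shorthand.** The same paragraph describes a failure on the primary endpoint as a patient without normalization, where the whole composite must be meant. This stands. A reader might infer that the plan certainly draws from the wrong rate, but the text supports only that the wording does not match the endpoint and needs clarifying. Even taken literally, the error pulls towards no effect (0.40-0.43 against 0.45) and would not create a positive result.

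**Most cells are not near-empty.** This also stands. Adult cells expect about 9-11 patients. Only the child cells are thin, and only if children are few, which the article does not say. Children enter only after a safety review of the first five treated adults, so a small share is plausible but not established.

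**The imputation does test the primary rule.** A reader might infer that this analysis cannot test the primary result. That is wrong: it replaces missing = failure with missing at random within cell, and it moves the risk difference from 0.36 to 0.45. The narrower criticism, that complete case already makes the same move, survives.

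**The loss of precision is modest.** The complete-case SE is itself about 4% low (0.132 against 0.138), and only a sensitivity analysis is affected. This is fair, and it limits the weight of the point.

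**Conditioning on V3 to V6 is a modelling choice.** V3 to V5 fall in titration, early dropouts lack V6, and many predictors within arms of about 25 would be unstable. This argues for a small model, not for using none of the patient's own values.

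**A tipping-point analysis is usually left to the analysis plan.** That is so, and its absence from the article is not an error. It is suggested here only because the two analyses that the article does fix share one assumption.

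**Conclusion.** The point holds in a limited form. The imputation rule as written names a proportion that does not match the composite endpoint, though it may be shorthand. It is also improper as multiple imputation, because no parameter uncertainty is drawn and an empty cell has no defined probability. And it sets aside calciuria values that the trial collects.

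The consequence is modest. A literal reading costs the fluconazole rate 1.5-3 points at 10% missing or 3-6 points at 20%. The SE is about 6-8% too small at 20% missing and 20% children. The estimate is nearly the same as complete case, and missingness related to response goes unexamined.

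All these sizes rest on assumed missing rates, shares of children, 1,25(OH)2D split and normalization rates, and the simulation assumes missingness completely at random. The primary estimate, its test and the 89% power are not touched.

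**What to change.** In the analysis plan, which the article says will be written before the database is frozen:

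1. State that the imputed outcome is the composite (normalization, or a fall of at least 30% from baseline).
2. Replace the cell-proportion draw with proper multiple imputation, including parameter draws, of log 24-h calciuria at W16. Keep the model small: arm, age class, 1,25(OH)2D category, baseline calciuria, and one on-treatment value (for example V6 or the last available).
3. Derive the composite in each imputed set, fit the primary model, and pool by Rubin's rules.
4. Add a tipping-point grid over the number of missing patients in each arm counted as successes, and report where the conclusion changes.

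The cost is wording, a little programming, and slightly wider intervals in one sensitivity analysis. No new data are needed.

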### Quality control

A Clinical Research Associate mandated by the sponsor will ensure the proper conduct of the study, collection of written data, their documentation, recording, and reporting, in conformity with the Good Clinical Practices as well as the current legal and regulatory provisions.

Furthermore, the investigators agree to accept the quality control audits carried out by persons mandated by the sponsor as well as inspections by the competent authorities. All data and all documents and reports may be the subject of regulatory audits and inspections without the possibility of using medical secrecy as opposition.

### Data safety monitoring board

An independent monitoring committee (DSMB) will be set up. The DSMB will authorize in association with the ANSM the enrollment of pediatric patients in the study (patients <18 years old), once inclusion of 5 adult patients treated during a minimum period of 10 weeks at stable dose (W_16_), in accordance with safety data collected in the study. The DSMB will evaluate the onset of potential mycological resistance among the study and monitor the unexpected adverse events.

It will be made of two specialists of nephrolithiasis, a pharmacologist, and an infectious disease specialist.

Further details can be found in the DSMB Charter (Additional file 3).

### Ethics

The study protocol was first approved by the Ethic committee EC Nord Ouest I on December 14th 2020 (20.09.22.57341), and then on June 17th 2021 (20.00146.057341-MS01) after substantial modifications and by the French competent authority (Agence Nationale de Sécurité du Médicament et des produits de santé, ANSM) on November 24th, 2020 (MEDAECPP-2020-09-00014) and then on June 30th 2021 (MEDMSANAT-2021-06-0053_2020-003011-97). This approval applies for all participating centers. It is registered under EudraCT number 2020-003011-97. The study is compliant with the reference methodology of Commission Nationale de l’Informatique et des Libertés. The study is conducted in accordance with the French legislation, the Good Clinical Practice, and the Declaration of Helsinki. Written consent will be obtained for all patients before inclusion, for their participation to the study research and for the constitution and the storage of a biocollection. For patients who have not yet had a genetic analysis, a specific genetic consent will be proposed, to perform genetic testing and to store corresponding samples, according to current practice.

For minor, consent of both parents (or legal guardian) is required.

The sponsor has subscribed to an insurance policy for the entire duration of the study, covering its own civil liability as well as that of all the doctors involved in the realization of the study. It will also insure the full compensation for harmful consequences of the research for the participating persons and their beneficiaries, except with evidence, at their responsibility, that the damage is not attributable to their mistake or to that of all consultants, without the possibility of being opposed to an act by a third party or the voluntary withdrawal of the person who had initially consented to participate in the research.

The insurance contract was signed before the start of the study with the *Société Hospitalière d’Assurance Mutuelle*, [name], under the number 159077.

During the research involving human individuals or at its end, the data collected on the persons participating and sent to the sponsor by the investigators (or any other specialists) will be made anonymous. The persons having direct access to the data will take all necessary precautions to ensure the confidentiality of the information related to the trials, to the persons participating and, in particular, with regard to their identity as well as the results obtained.

In the event that a substantial modification is made to the protocol by the investigator, it will be approved by the sponsor. Before its implementation, the latter must obtain a favorable opinion from the EC and an authorization from the ANSM within the scope of their respective competencies. The coordinating investigator and coordinating center will then notify the other centers and the sponsor will update the protocol in the clinical trial registry.

